## Monitoring

### Data safety monitoring committee

A data safety monitoring board (DSMB) will be formed that include two nephrologists from outside the study team, as well as an independent statistician. The DSMB will conduct a safety review of the study when half the participants have finished their first run-in period and then every 3 months until trial completion. The DSMB will be primary focused on participant safety, but will also review study progress and conduct. As this is a trial there will be no prespecified stopping criteria. As this is a short-term crossover trial there will be no prespecified stopping criteria.

### Interim analyses

The trial will be continued until all recruited participants have reached the end of their follow-up and data have been collected, processed and cleaned. There are no plans for early termination unless a pattern of hyperkalaemia is seen in the run-in period and the DSMB and or qualified investigator recommends early termination due to risk.

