### Criteria for discontinuing or modifying allocated interventions

Each participant has the right to withdraw from the trial at any time. Participants may discontinue trial participation at any time and are requested to contact a research team member to inform them of their decision. In addition, the Investigator may discontinue a participant from the trial at any time if the investigator considers it necessary for any reason including:

Pregnancy.Ineligibility.Significant protocol deviation.Significant non-compliance with the protocol.Disease progression which results in inability to continue with the protocol.Withdrawal of consent.Loss to follow-up.Significant elevated risk due to hyperkalemia.

Withdrawal will not result in exclusion of the data for that participant from analysis. As the primary analysis will be based on an intention-to-treat there will also be a completer only analysis performed. If the participant is withdrawn within the first two weeks of the trial they will be replaced. If the replacement participant is withdrawn there will be no subsequent replacement. The reason for withdrawal will be recorded in the case report form (CRF), if provided.

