### Relevant concomitant care permitted or prohibited during the trial

All participants enrolled in the study will continue to receive multidisciplinary CKD care during and after the trial. Patients that are already on potassium binding therapy will be excluded from this trial. If it is determined that a participant needs to start potassium binding therapy they will be withdrawn from the trial and the reason for withdrawal will be recorded.

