### Outcomes

The primary outcome is evaluating sK concentration during the five timepoints at week 0, 1–2, 8, 10 and 16. The secondary outcomes include assessing health related quality of life through KDQOL-SF and STS5 which will be assessed throughout the trial, analyzing clinical chemistry systolic and diastolic blood pressure, and assessing dietary data using the information received from ASA24. Clinical chemistry will look at sodium, potassium, urea, phosphate, and the albumin/creatinine ratio in the urine alongside the collection of blood samples for serum potassium, hemoglobin A1C, albumin, bicarbonate, calcium, chloride, creatinine, eGFR, glucose, phosphorus, sodium and blood urea nitrogen measurement. All samples will be collected and processed by the Diagnostic Services of Manitoba. Individuals will be scheduled for an in-person visit which will include a clinical exam and blood sample to monitor serium potassium and bicarbonate during weeks 1 or 2. Secondary outcome measures will be measured on week 0, 8, 10 and 16. Additionally, anthropometric measurements such as height, weight and BMI will be collected at baseline alongside blood pressure in triplicate.

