### Participant timeline

See Appendix A.

For the first two weeks, all participants will start on a liberalized potassium run-in period. Following the run-in period, the participants will be randomized to either the experimental group or the standard care group for six weeks. After the six weeks, a crossover will occur after a two-week washout period.

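### The only named ground for stopping the trial, a pattern of hyperkalaemia, is limited to the run-in, although 75% of planned liberalized exposure comes later

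*Protocol article*

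**What the plan says.** Under Interim analyses, the protocol article commits to continuing until everyone has completed follow-up. It foresees no early stop "unless a pattern of hyperkalaemia is seen in the run-in period and the DSMB and or qualified investigator recommends early termination due to risk".

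Under Data safety monitoring committee, the board reviews safety "when half the participants have finished their first run-in period and then every 3 months until trial completion". The same section adds: "As this is a short-term crossover trial there will be no prespecified stopping criteria". The Interim analyses sentence is therefore the only place where a trial-level ground for stopping is named.

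On exposure, Participant timeline states: "For the first two weeks, all participants will start on a liberalized potassium run-in period". After that, "the participants will be randomized to either the experimental group or the standard care group for six weeks", and they cross over following a two-week washout. Under Outcomes, the primary outcome is described as "evaluating sK concentration during the five timepoints at week 0, 1–2, 8, 10 and 16".

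Two provisions protect the individual. The investigator may discontinue a participant for "Significant elevated risk due to hyperkalemia" (Criteria for discontinuing or modifying allocated interventions). The section on concomitant care adds: "If it is determined that a participant needs to start potassium binding therapy they will be withdrawn from the trial".

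**The concern.** The named ground covers the shorter and earlier part of the exposure it is meant to guard against. Run-in potassium is checked once, at week 1 or 2, so it reflects at most two weeks on the diet. The only scheduled values taken after a full six-week liberalized period are those at week 8 (liberalized diet first) and week 16 (liberalized diet second). A pattern of hyperkalaemia in those values falls outside the wording.

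The board keeps meeting after most run-ins are over. At its early reviews it would hold end-of-period values from randomized liberalized periods while other participants had yet to start or finish theirs. An end-of-period value comes too late for the person who gave it, but it bears on the decision for those still to be exposed. A board or investigator acting on it would be acting outside the only ground the protocol plans for.

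**Working it through.** The protocol gives no figure of its own on this point, so there is none to reproduce.

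**Inputs from the protocol article**
- 30 participants, predicted to enrol at one per week (Recruitment).
- Two-week liberalized run-in for all, then two six-week periods separated by a two-week washout (Participant timeline). This gives run-in weeks 0–2, period 1 weeks 2–8, washout weeks 8–10 and period 2 weeks 10–16.
- First board review when half the participants have finished the run-in, then every 3 months (Data safety monitoring committee).
- 1:1 sequences, stratified by sex, blocks of 2 (Sequence generation).

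**Share of exposure outside the wording**
- Run-in: 30 × 2 = 60 participant-weeks.
- Randomized liberalized period: 30 × 6 = 180.
- Share after the run-in: 180 / (60 + 180) = 180/240 = 75%.
- If 10% of participants never contribute a randomized liberalized period (assumed): 162/222 = 73%. If 20%: 144/204 = 71%.

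**Calendar of reviews**

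Assume one enrolment per week from week 0, so that e = 0, 1, …, 29 is the enrolment week, and take 3 months as 13 weeks. The 15th run-in ends at 14 + 2 = week 16. Reviews then fall at weeks 16, 29 and 42. The last run-in ends at 29 + 2 = week 31 and the last participant finishes at 29 + 16 = week 45.

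**Randomized liberalized exposure at each review**

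The randomized liberalized interval is e+2 to e+8 (liberalized first) or e+10 to e+16 (standard first). At review week R, the weeks accrued by one participant are min(6, max(0, R − e − 2)) or min(6, max(0, R − e − 10)).

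Example for R = 16, sequences alternating and liberalized first at e = 0:
- Liberalized-first (even e): five participants have all 6 weeks (30), and e = 10 and e = 12 have 4 and 2. Sum 36.
- Standard-first (odd e): e = 1, 3, 5 have 5, 3 and 1. Sum 9.
- Total 36 + 9 = 45 accrued, and 180 − 45 = 135 ahead.

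| Review | Accrued | Ahead | Participants with exposure ahead | Completed liberalized periods | Run-in weeks accrued |
|---|---|---|---|---|---|
| Week 16 | 45 | 135 | 25 | 5 | 31 |
| Week 29 | 123 | 57 | 12 | 18 | 57 |
| Week 42 | 176–178 | 2–4 | 1–2 | 28–29 | 60 |

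The ranges at week 42 depend on which sequence comes first; weeks 16 and 29 are the same either way. At week 29, 57/180 = 32% of the randomized liberalized exposure is still ahead. Randomized periods supply 123 of the 123 + 57 = 180 liberalized participant-weeks the board would then be looking at.

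**Sensitivity to sequence order**

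In 5,000 simulated allocations (blocks of 2 within sex, 15 of each sex assumed, random arrival order), the central 95% range of participant-weeks ahead was 130–140 at week 16, 52–62 at week 29 and 0–6 at week 42. This varies only the order of sequences, not the enrolment rate or dropout.

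**The case against.** The strongest reply is that the sentence describes what is foreseen and does not bind the board. Having no plans to stop is not a ban on stopping, and the board's safety reviews run to the end of the trial. Individual discontinuation, withdrawal for binder need and adverse-event follow-up (Harms) all remain. A condensed article may also leave the board's remit to a charter. All of this stands, and it is why the point is about wording and not about a missing safeguard. It does not explain why a protocol that chose to name a ground limited it to the run-in.

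A second reply is that a pattern is seen in potassium values, not in participant-weeks. Each participant has one scheduled on-diet run-in value and one end-of-liberalized value, so the split is 30 to 30. Run-in values outnumber the others at the first two reviews: about 15–16 against 5 at week 16, and 28–29 against 18 at week 29. The count is right. On that measure half of the scheduled values still lie outside the wording, and they are the only ones taken after six liberalized weeks.

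Third, the practical reach is limited. Five values at week 16 are a thin basis for a pattern, and by week 42 almost nothing is left to prevent. The calendar also rests on predicted enrolment. These points stand and limit the size of the benefit.

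Fourth, the week 8 and week 16 values feed the primary comparison, so naming them in the rule means showing the board outcome data by diet. A safety board may review such values, and its own independent statistician can hold the labels. The study statistician then stays blinded, as the Blinding section requires.

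**Conclusion.** The concern holds. The one trial-level ground for stopping that the protocol names is confined to the run-in, which is 60 of 240 planned liberalized participant-weeks. The other 180 (75%) are outside it. That figure needs only the design with 30 participants and full follow-up, and it falls to 71–73% under the assumed dropout.

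The practical consequence is concentrated at the reviews near weeks 16 and 29, with 135 and 57 randomized liberalized participant-weeks still ahead. It is negligible near week 42. Those figures assume one enrolment per week, 13-week review intervals, alternating sequences and no dropout or replacement.

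The severity is low: the board keeps its discretion and the individual protections are intact. It is a cheap improvement to a stated rule.

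**What to change.** In the Interim analyses section, replace the restriction to the run-in with: *during any liberalized-potassium exposure (run-in or randomized periods)*. Leave the rest of the sentence, including the need for a recommendation from the board or the qualified investigator, as it is. Board reviews would then draw on the already scheduled week 8 and week 16 potassium values and the adverse events, as well as the week 1–2 check.

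No visit, blood draw, threshold or gating step is added, and the decision to set no prespecified stopping criteria stands. Planned sample size and power do not change. The costs are a protocol wording change, a slightly higher chance of early termination, and the need to give the board potassium values labelled by diet. The board's independent statistician can hold that labelling.

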### Harms

All adverse events (AE) occurring during the trial that are observed by the Investigators or reported by the participant will be recorded on the CRF, whether or not attributed to trial intervention. The following information will be recorded: description, date of onset and end date, severity, assessment of relatedness to trial intervention. Follow-up information should be provided as necessary. In case any adverse event is reported, patients will be offered to be seen in the next available clinic visit or within one week, whichever is earlier, and will continue to be followed in the clinic until the AE is resolved [16]. The severity of events will be assessed on the following scale: 1 = mild, 2 = moderate, 3 = severe. AEs considered related to the trial intervention as judged by the Qualified Investigator will be followed either until resolution or the event is considered stable. In case AEs result in withdrawn from the trial, the patients that are withdrawn due to adverse treatment reaction will also be followed by the CKD clinic until the AEs has resolved [16].

### Monitoring of trial conduct

Regular monitoring will be performed according to good clinical practices (GCP) by the principal investigators or a delegate. A subset of all data will be evaluated for compliance with the protocol and accuracy in relation to source documents. Following written standard operating procedures, the monitoring will verify that the clinical trial is conducted and data are generated, documented and reported in compliance with the protocol, GCP and the applicable regulatory requirements [16].

## Ethics and dissemination

### Research ethics approval

DK-Lib CKD has received approval from the University of Manitoba Health Research Ethics Board (HS25191 (B2021:104)). All amendments to this studies protocol are reviewed and approved by the University of Manitoba Biomedical Research Ethics Board and changes to the protocol are updated on clinicaltrials.gov (NCT05090865).

### Protocol amendments

The University of Manitoba Research Ethics Board will be responsible for approving and signing off the trial protocol and any protocol amendments. Before any participants are enrolled into the study, the PI at each site is required to obtain local approvals and agreements with Shared Health Manitoba and the University of Manitoba.

### Who will take informed consent

The participant must personally sign and date the latest approved version of the Informed Consent form through the REDCap online platform before any trial specific procedures are performed. Informed consent will be obtained from all subjects and/or their legal guardian(s) that are interested in participating in the study. This will be done by the study coordinator and/or students who are GCP certified and have received the appropriate training on how to take informed consent.

Participants will be asked to attend a virtual or in-person consent visit, depending on regional COVID-19 restrictions.

### Additional consent provisions for collection and use of participant data and biological specimens

Clinical chemistry outcomes at baseline, week 1–2, 8, 10 and 16, will be captured from the participant’s nephrology clinic records or a requisition will be sent to participants directly from clinic. All samples will be collected and analyzed by Shared Health Diagnostics at both Health Sciences Centre and Seven Oaks Hospital.

### Confidentiality

The trial staff will ensure that the participants’ anonymity is maintained. The participants will be identified only by a participant ID number on all trial documents (except the email addresses on REDCap, remuneration forms, consent form and the study master list) and any electronic database. All documents will be stored securely and only accessibly by trial staff and authorized personnel. The trial will comply with The Personal Health Information Act (PHIA) or The Freedom of Information and Protection of Privacy Act (FIPPA) of Manitoba.

### Access to data

In addition to the research team and individuals from their institutions (Chronic Disease Innovation Centre, Centre for Healthcare Innovation, Health Sciences Centre and University of Manitoba) direct access will be granted to authorized representatives from the Sponsor, host institutions and the regulatory authorities to permit trial-related monitoring, audits and inspections.

### Post-trial care

Participants will continue to be followed by their nephrologist post trial.

### Dissemination policy

A meeting will be held after the end of the trial to allow discussion of the main results among the collaborators prior to publication. The results of the trial will be submitted for to conferences for presentation and for publication in a peer reviewed journal.

## Discussion

The findings of this study may provide additional data to help inform dK recommendations in patients with CKD. This study will also help increase our understanding of how dietary restrictions are implemented and the effects these restritions can have on people’s quality of life. The findings of this study may also help inform other dietary interventions in CKD, such as the use of fruit and vegetables as dietary bicarbonate sources in the treatment of metabolic acidosis, for which the perceived risk of hyperkalemia may be a barrier for practioners and people living with CKD.

## Data Availability

Not applicable; this is a study protocol.

## Abbreviations

AE: Adverse event
ASA24: Automated Self-Administered 24-hour Canada dietary assessment tool
BMI: Body mass index
CKD: Chronic Kidney Disease
CRF: Case report form
dK: Dietary potassium
DSMB: Data Safety Monitoring Board
eGFR: Estimated glomerular filtration rate
ESRD: End stage renal disease
FIPPA: Freedom of Information and Protection of Privacy Act
GCP: Good clinical practices
K: potassium
KDQOL-SF: Kidney Disease Quality of Life Short Form
PHIA: Personal Health Information Act
PI: Prinicpal investigator
RAASi: Renin-angiotensin-aldosterone system inhibitors
RCT: Randomized controlled trial
RD: Registered dietitian
SGLT2i: Sodium-glucose cotransporter 2 inhibitors
sK: Serum potassium
STS5: Sit-to-stand five times
